##### Sample size calculation

For dichotomous variable and superior clinical design, the sample size was determined using the following formula to calculate the sample size [29, 30, 31]:

$$N = 2 \times \left( {\frac{{Z_{1 - \alpha } + Z_{1 - \beta } }}{{d - \delta_{0} }}} \right)^{2} \times p \times (1 - p)$$,

where the null hypothesis H_0_: T–S = δ;

the alternative hypothesis H_1_: T–S > δ;

And test statistics: Z = (d–δ)/sd.

In the equation, N represents the size of the group. p indicates the response rate of the control group and p_0_ denotes the response rate of the treatment group. Z_x_ represents the normal standard deviation for a one- or two-sided x. d represents the real difference between the two treatment effects. δ_0_ indicates a clinically acceptable margin. S^2^ indicates the pooled standard deviation of both comparison groups. T represents the treatment group (modern medicine + TCM treatment). S is the control group (modern medicine + TCM placebo). δ indicates the clinically admissible margin of superiority. d represents the effectiveness difference between T and S (d =| p_0_—p |). sd represents the standard error of d. Z = Z obeys the normal standard distribution. α represents type I error, β represents type II error, and 1 − β indicates the power.

In this study, α = 0.05, β = 0.20, δ_0_ = 0.10, 1 − β = 0.80, Z_1−α_ = 1.64, Z_1−α_ = 1.28, and based on literature, *P*_0_ = 0.767 and *P* = 0.533[29]. Hence, a value of *N* = 233 was calculated. The failure to follow-up rate was considered to be 10% and accordingly, *N* = 233 × (1 + 10%) = 257. Lastly, the number of subjects each in the treatment and control groups is 257, which led to a total of 514 individuals in this study.

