#### Principles of data analysis

Statistical analysis will be performed using the SAS Analytics Software Solutions (version 9.4, SAS Institute Inc., Cary, North Carolina 27,513, US). Odds ratio (OR) and 95% confidence interval (*CI*) of categorical variables will be calculated using two-tailed Chi-square test, and Fisher’s exact test will be used to compare the differences in qualitative variables between the two groups. Quantitative variables will be described as the mean, median, standard deviation, or inter-quartile range, and analyzed using the rank-sum test, t-test, analysis of variance (ANOVA), repeated measurement ANOVA, generalized linear mixed model (GLMM), and generalized estimation equation (GEE). Differences will be considered significant at *P* < 0.05 with two-tailed test.

This study will be conducted across several research centers; some subjects from the same center, it may produce similarity or homogeneity. The methods that will be considered for adjusting for effects of the center will include the Breslow-Day method, Cochran-Mantel–Haenszel statistics (CMH), and logistical regression, whereas GEE and GLMM will be used for data mining. In addition, confounding factors will be considered in all data analysis, it will include gender, age, and other lung diseases.

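### The sample-size formula gives both arms the control arm's variance, which does not match the standard error of the difference in its own test statistic; the error is conservative and worth 2.2 to 3.6 points of power

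*Protocol article*

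**What the plan says.** All of the design material is in the Sample size calculation section of the protocol article.

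- The formula is N = 2 × ((Z₁₋α + Z₁₋β)/(d − δ₀))² × p × (1 − p). The symbols are defined by "p indicates the response rate of the control group and p_0_ denotes the response rate of the treatment group". The treatment rate enters only through d.
- The alternative is one-sided against a margin: "the alternative hypothesis H_1_: T–S > δ". The test statistic is Z = (d − δ)/sd, and "sd represents the standard error of d".
- A further quantity is defined and then not used in the formula: "S^2^ indicates the pooled standard deviation of both comparison groups".
- The inputs are "α = 0.05, β = 0.20, δ_0_ = 0.10, 1 − β = 0.80", with "Z_1−α_ = 1.64, Z_1−α_ = 1.28" and assumed rates of 0.767 (treatment) and 0.533 (control).
- The results are 233 per group, 257 after adding 10% for loss to follow-up, and 514 in total.

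The Principles of data analysis section sets a different sidedness: "Differences will be considered significant at *P* < 0.05 with two-tailed test". Neither that section nor Data analysis of the main outcome measure mentions the margin.

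**The concern.** The standard error of a difference between two independent proportions depends on both rates. The formula uses one rate for both arms, while the same section assumes rates 0.234 apart and writes a test that divides by the standard error of that difference. The margin does not help: the null places the rates 0.10 apart, so a single common rate describes neither the null nor the alternative.

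At stake is whether the power given for the primary comparison belongs to the test described beside it. The variance term is also independent of the choice of quantiles. A sponsor who corrected only the quantile would still publish a power figure that does not match the written statistic.

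**Working it through.** **Inputs**, all from Sample size calculation: p = 0.533, p₀ = 0.767, d = 0.767 − 0.533 = 0.234, δ₀ = 0.10, d − δ₀ = 0.134, z-values 1.64 and 1.28. Evaluable patients per group: 257 × 0.90 = 231.3, taken as 231.

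**Step 1: reproduce the printed N.** With 2 × 0.533 × 0.467 = 0.4978,

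N = (2.92/0.134)² × 0.4978 = 236.4.

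This is close to the printed 233 but not equal to it. Rounding 0.134 to 0.135 gives 232.9, which is a possible explanation that the document does not confirm. At the same z-values the pooled variance gives 216.1 and the unpooled variance 203.1. The control-arm variance was therefore actually used; the symbol is not merely mislabelled.

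**Step 2: variance factors for the written statistic.**

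- Formula as printed: 2 × 0.533 × 0.467 = 0.4978
- Unpooled, p(1 − p) + p₀(1 − p₀): 0.2489 + 0.1787 = 0.4276
- Pooled, with mean rate (0.533 + 0.767)/2 = 0.65: 2 × 0.65 × 0.35 = 0.4550

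The printed factor is 0.4978/0.4276 = 1.16 times the unpooled factor and 0.4978/0.4550 = 1.09 times the pooled one.

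**Step 3: N and power.** N = (2.92/0.134)² × V. Power = Φ(0.134/√(V/231) − 1.645), for the section's one-sided 0.05 test against the 0.10 margin.

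| Variance | V | N per group | 0.134/√(V/231) | Power at 231 |
|---|---|---|---|---|
| As printed | 0.4978 | 236.4 | 2.89 | 89.3% |
| Pooled | 0.4550 | 216.1 | 3.02 | 91.5% |
| Unpooled | 0.4276 | 203.1 | 3.11 | 92.9% |

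The understatement is 91.5 − 89.3 = 2.2 points (pooled) or 92.9 − 89.3 = 3.6 points (unpooled), taken from the rounded percentages.

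**Step 4: separate the variance from the quantile.** The quantile for 80% power is 0.84; 1.28 belongs to 90%. Keeping the control-arm variance and using 0.84:

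N = (2.48/0.134)² × 0.4978 = 170.5, or 171 per group.

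The quantile slip therefore adds 236.4 − 170.5 = 65.9 per group. The variance term adds 236.4 − 203.1 = 33.3 (unpooled) or 236.4 − 216.1 = 20.3 (pooled).

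**Step 5: correct the quantile alone.** At 171 per group the formula reports 80%. The test using the standard error of d would have 83.0% (pooled) or 85.0% (unpooled). The mismatch remains after the quantile is put right.

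**The case against.** The strongest reply is that this is a cautious planning approximation. At these rates the control variance is the larger one, so the formula asks for about 20 to 33 more patients per group than the written statistic needs, and power is protected. That stands. Nothing here suggests that the trial is too small.

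The effect is also small beside the uncertainty in the assumed rates. If d were 0.224 instead of 0.234, with the printed variance, one-sided power at 231 per group would fall from 89.3% to Φ(0.124/√(0.4978/231) − 1.645) = 84.8%, a shift of 4.5 points. That stands too, and it limits the weight of the point. It does not make the formula agree with the statistic.

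Nor does the document fix the correct variance. It prints no expression for sd, and the unused pooled quantity points towards the smaller discrepancy. The supported effect is therefore a range. The printed N matches neither end of it.

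Two stronger readings are tempting and are not supported:

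- A reader might infer that the variance term explains why the stated 80% does not fit. With the formula's own variance, one-sided power is already 89.3%; most of that gap comes from the 1.28.
- A reader might quote a larger effect by applying a two-tailed 0.05 level to the margin test: 82.3% as printed, 85.5% pooled, 87.6% unpooled, a difference of up to 5.3 points. That joins the margin of one section to the sidedness of another, a test that neither section describes.

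Finally, the analysis sections name chi-square, Cochran-Mantel-Haenszel, GEE and logistic regression without a margin. Repairing the formula therefore does not by itself yield the power of the planned analysis. That mismatch is separate, and it is why the restated power must name its test.

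**Conclusion.** The point holds as a secondary, conservative inconsistency within the Sample size calculation section. The control arm's variance is applied to both arms, while the section's own statistic needs the variance of a difference between two unequal rates. At the printed z-values this means 236 per group instead of 203 (unpooled) or 216 (pooled). For the one-sided margin test at 231 evaluable per group it understates power by 2.2 to 3.6 points.

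These sizes assume the document's rates and margin, the normal approximation, and a loss of exactly 10% from 257 per group. They do not show an underpowered trial, and they give no reason to change the enrolment target.

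**What to change.** - Replace 2 × p × (1 − p) with p(1 − p) + p₀(1 − p₀). If the pooled quantity is what was meant, use 2 × p̄ × (1 − p̄) with p̄ the mean of the two rates, and say so. Give the expression for sd, and either use S² or delete it.
- Correct the second z-value and its label in the same edit, so that quantile and stated power agree. Show the arithmetic behind N, since the printed inputs give 236 and not 233.
- Keep 514 patients. Restate the power at 231 evaluable per group and name the test it refers to: margin or no margin, one-sided or two-sided. For the one-sided 0.05 test against the 0.10 margin it is 92.9% unpooled or 91.5% pooled. If the primary analysis is to be two-tailed without the margin, the power statement should be calculated for that test instead.

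The cost is one formula and a few sentences. Recruitment, randomisation and conduct are unaffected.

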#### Data analysis of the main outcome measure

The main outcome measure is treatment effect, and this categorical variable includes improvement, stabilization, and deterioration. Stabilization and deterioration will be merged into a new variable, namely non-improvement. Hence, this three-level classification will comprise merged binary variables and include improvement and non-improvement. For this dichotomous variable, Breslow-Day method, CMH, GEE, and logistic regression will be utilized to compare curative effects between the two groups.

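### The trial is sized for superiority by more than a 10-point margin, but the named primary analysis does not carry that margin forward

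*Protocol article*

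**What the plan says.** **Sample size calculation.** The hypotheses are written with a shifted null: "where the null hypothesis H_0_: T–S = δ" and "the alternative hypothesis H_1_: T–S > δ". The section then gives "And test statistics: Z = (d–δ)/sd" and explains that "δ indicates the clinically admissible margin of superiority". The inputs include "α = 0.05, β = 0.20, δ_0_ = 0.10" and "Z_1−α_ = 1.64, Z_1−α_ = 1.28". The assumed response rates are 0.767 (treatment) and 0.533 (control). The result is 233 per group, raised to 257 per group (514 in total) for 10% loss to follow-up.

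**Data analysis of the main outcome measure.** The three-level outcome is collapsed to improvement against non-improvement, and then: "For this dichotomous variable, Breslow-Day method, CMH, GEE, and logistic regression will be utilized to compare curative effects between the two groups".

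**Principles of data analysis.** Categorical outcomes are to be reported as odds ratios with 95% confidence intervals. The decision rule reads "Differences will be considered significant at" P below 0.05, two-tailed.

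Neither analysis section mentions 0.10, a risk difference, or the statistic printed in the sample size section.

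**The concern.** The hypothesis and the sample size concern one question (is the combination better by more than 10 percentage points?). The named methods and decision rule, on their usual null, answer a weaker one (is there any difference?). The scale changes from risk difference to odds ratio, and the sidedness changes from a one-sided 1.64 to a two-tailed test.

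What is at stake is the meaning of a significant primary result. The trial could report success with an observed difference below its own margin, and a reader of the sample size section would take that as rejection of the stated null. Alternatively, if no margin is meant, the only justification given for 514 participants belongs to a test that the analysis sections do not plan.

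**Working it through.** **Inputs.** From Sample size calculation: control rate p = 0.533, treatment rate p₀ = 0.767, so d = 0.234; margin 0.10; Z values 1.64 and 1.28; 257 per group with 10% loss. The section uses both δ and δ₀ and gives a value only for δ₀. I take δ = δ₀ = 0.10. Evaluable per arm: 257 × 0.90 = 231.

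**1. Does the stated size depend on the margin?** The protocol's formula is N = 2 × ((Z₁ + Z₂)/(d − δ₀))² × p(1 − p), with p(1 − p) = 0.533 × 0.467 = 0.2489.
- With the margin: 2 × (2.92/0.134)² × 0.2489 = 236.4, within 1.5% of the stated 233.
- Without it: 2 × (2.92/0.234)² × 0.2489 = 77.5.

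So the margin about triples the trial. (The printed 1.28 corresponds to 90% power although β = 0.20 is stated. That is a separate matter and does not affect this point.)

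**2. What does each named method test?** CMH, logistic regression and GEE usually have odds ratio = 1 as the null, which is zero difference. Breslow-Day tests whether odds ratios are homogeneous across centres, so it tests neither zero difference nor the margin. A 10-point margin has no fixed odds-ratio equivalent. At 53.3% control it would be (0.633/0.367)/(0.533/0.467) = 1.51, and no such value is given.

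**3. Smallest significant observed difference (231 per arm, control 53.3%).**
- Against zero, two-sided 5%, pooled variance. At 62.3% against 53.3% the mean is 0.578, SE = √(2 × 0.578 × 0.422/231) = 0.0460, and 1.96 × 0.0460 = 0.090. Threshold: about **9.0 points**.
- Against 0.10, one-sided 5%, unpooled variance. At 70.6%, SE = √((0.2489 + 0.2076)/231) = 0.0445, and 0.10 + 1.645 × 0.0445 = 0.173. Threshold: about **17.3 points**.
- Against 0.10, two-sided 5%, unpooled variance. At 72.0%, SE = √((0.2489 + 0.2016)/231) = 0.0442, and 0.10 + 1.96 × 0.0442 = 0.187. Threshold: about **18.7 points**.

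Observed differences from about 9 to 17 points would therefore be significant as planned without rejecting the stated null.

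**4. Rejection rate at a true 10-point difference (53.3% against 63.3%).** The SE under the zero null is √(2 × 0.583 × 0.417/231) = 0.0459, so the critical difference is 0.0899. The SE under the true rates is √((0.2489 + 0.2323)/231) = 0.0456. Then Φ((0.10 − 0.0899)/0.0456) = Φ(0.22), about **59%**. With all 257 per arm evaluable it is 63%.

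**5. Power at the assumed rates (231 per arm).**
- Zero null: 0.234/0.0430 = 5.4 standard errors, so power is above 99%. For 80% power, n = (1.96 + 0.84)² × (0.2489 + 0.1787)/0.234² = 61.2, that is **62 per arm** (65 with pooled variance under the null).
- Margin null, unpooled SE 0.0430: 0.134/0.0430 = 3.11, giving 93% (one-sided 5%) or 88% (two-sided 5%).
- Margin null, control-rate variance as in the protocol's formula, SE 0.0464: 0.134/0.0464 = 2.89, giving 89% or 82%.

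**The case against.** A reader might infer that the stated hypothesis will never be tested. The document does not go that far. The sample size section prints the margin statistic beside the hypotheses, the analysis section states no null value, and the zero null is inferred from the usual default of the methods and the two-tailed rule. The link between a method and a success margin is also often left to a statistical analysis plan, and none is shown. This tempers the wording but does not remove the conflict: the article itself names the primary methods, the effect measure and the significance rule, and they do not match the hypotheses that it also states.

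The stronger objection is that no margin may be intended. The Hypothesis and Aim of the study sections ask only whether adding TCM improves on modern medicine, and a test against zero answers that. The margin appears only in the sample size section, so an ordinary superiority trial sized with a margin formula is a plausible reading. This stands. It means that the 59% cannot be presented as an unconditional type I error rate.

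Nor can it be said that the hypothesis as registered is at risk, because no registry record is at hand. It would likewise be too broad to say that every listed method tests an odds ratio of 1, since Breslow-Day does not.

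**Conclusion.** The point holds as an internal contradiction about the primary hypothesis, in both margin and sidedness. Its consequence depends on intent:

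- **Margin intended.** The planned test rejects the stated null about 59% of the time when the true difference sits exactly on it, against a nominal 5%. Success could be declared from about 9.0 observed points, when about 17.3 (one-sided) or 18.7 (two-sided) are needed.
- **Ordinary superiority intended.** The planned test keeps its 5% error rate. The stated hypothesis, N and power are then wrong for the analysis: about 62 per arm would give 80% power, and 231 per arm gives above 99%.

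The figures assume 231 evaluable per arm, a control rate of 53.3%, no centre effect and normal approximations. With 257 evaluable per arm the three thresholds become about 8.5, 16.9 and 18.2 points, so the conclusion does not change. The documents do not settle which intent is right, and that choice should not be left until the data are seen.

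**What to change.** Reconcile the three sections before unblinding, by one of two routes.

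**(a) Keep the margin.** Make the primary test a risk difference in improvement and claim superiority by the margin only if its lower confidence limit exceeds 0.10. State the sidedness. Report the test against zero as a separate, weaker statement. A centre-stratified (for example Mantel-Haenszel) estimate at month 12 would suit the centre-stratified randomisation and the 12-month treatment period. Both are proposals: the protocol names no primary visit, and its own Z statistic would also reconcile the text. Cost: new analysis wording and a stricter success criterion. Power at 231 per arm is about 89–93% at one-sided 5% and 82–88% at two-sided 5%.

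**(b) Drop the margin.** Remove δ and δ₀ from the hypotheses, statistic and formula, keep the test against zero, and restate the power (above 99% at the assumed rates). Cost: this is more than a change of wording, because it removes the stated basis for 233 per group. The sample size then needs a new justification, such as a smaller effect worth detecting.

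### The sample-size paragraph states 80% power but sizes with the 90%-power quantile, and sizes one-sided for a two-tailed analysis; the stated power is too low for the design as sized

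*Protocol article*

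**What the plan says.** Under Sample size calculation, the protocol article gives a formula for superiority by a margin on a binary outcome: N per group = 2 × ((Z for alpha + Z for beta)/(d − δ0))² × p(1 − p), where p is the control response rate. The hypothesis is directional: "the alternative hypothesis H_1_: T–S > δ". The error rates and margin are "α = 0.05, β = 0.20, δ_0_ = 0.10, 1 − β = 0.80", and the quantiles are "Z_1−α_ = 1.64, Z_1−α_ = 1.28". The assumed response rates are 0.767 (treatment) and 0.533 (control).

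The reported result is 233 per group. Loss is then added: "The failure to follow-up rate was considered to be 10% and accordingly" 233 is multiplied by 1.10, giving 257 per group and 514 in total.

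Under Principles of data analysis, the testing rule is two-sided: "Differences will be considered significant at" P < 0.05 "with two-tailed test". The section on the main outcome measure compares improvement with non-improvement by Breslow-Day, CMH, GEE and logistic regression. Neither analysis section mentions the 0.10 margin.

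**The concern.** Three things in the text do not fit together.

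- **Power.** Beta 0.20 calls for 0.84. The calculation uses 1.28, which belongs to beta 0.10. Because the second quantile carries the alpha label, the text never identifies 1.28 as the power term.
- **Sidedness.** 1.64 is a one-sided 5% quantile. The analysis section's two-tailed 5% rule corresponds to 1.96.
- **Hypothesis.** The sizing tests against a difference of 0.10. The planned analyses, as described, test against no difference.

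The sample size is the quantitative case for giving 514 patients 12 months of treatment, and a reader cannot tell from the text which alpha and power it was built on. The alpha conflict also reaches the final inference: a one-sided P of 0.04 would meet the criterion used for sizing and fail the one written for the analysis.

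**Working it through.** **Inputs (all from Sample size calculation).** Treatment rate 0.767, control rate 0.533, so d = 0.234. Margin 0.10, so d − δ0 = 0.134. Variance term p(1 − p) = 0.533 × 0.467 = 0.2489; doubled, 0.4978.

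**1. Reproduce the plan's figure.** With the printed quantiles:

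2 × ((1.64 + 1.28)/0.134)² × 0.2489 = 236.4, i.e. 237.

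The stated 233 is about 1.5% lower. If 0.134 is rounded to 0.135, the formula gives 232.9, i.e. 233. That rounding is an assumption; the document does not show the step.

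**2. Use the stated beta instead.**

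| Alpha | Quantiles | N per arm |
|---|---|---|
| One-sided 0.05 | 1.64 + 0.84 | 170.5, i.e. 171 |
| One-sided 0.05, more decimals | 1.645 + 0.842 | 171.4, i.e. 172 |
| Two-sided 0.05 | 1.96 + 0.842 | 217.6, i.e. 218 |

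None of these is near 233, so 1.28 was used in the calculation and is not just a misprint. As a check, Φ(1.28) = 0.8997, i.e. 90% power.

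**3. Loss to follow-up.** 233 × 1.10 = 256.3, i.e. 257. After 10% loss, 257 × 0.90 = 231.3, i.e. 231 evaluable. Dividing instead gives 233/0.90 = 258.9, i.e. 259.

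**4. Power of the trial as sized, against the 0.10 margin, with 231 evaluable per arm.**

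Control-rate variance, as in the plan's formula: SE = √(0.4978/231) = 0.0464 and 0.134/0.0464 = 2.887.

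- One-sided 0.05: Φ(2.887 − 1.645) = 89.3%
- Two-sided 0.05: Φ(2.887 − 1.96) = 82.3%

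Unpooled variance: 0.533 × 0.467 + 0.767 × 0.233 = 0.4276, SE = √(0.4276/231) = 0.0430 and 0.134/0.0430 = 3.114.

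- One-sided 0.05: 92.9%
- Two-sided 0.05: 87.6%

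With 233 evaluable and control-rate variance the figures are 89.5% and 82.6%, so the choice of loss inflation hardly matters.

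**5. Power against no difference.** With the same rates and control-rate variance, two-sided 0.05: Φ(0.234/0.0464 − 1.96) ≈ 99.9%. The figures in step 4 therefore apply only if the 0.10 margin is actually tested.

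**The case against.** The case for leaving the paragraph alone is that nothing harmful follows from the slip. Most of that case stands: 80% power is met under either sidedness even after 10% loss, so the error is on the safe side, and two-sided the gap is only 82% against 80%.

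Four stronger readings are tempting, and the document does not support them.

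- *233 has no derivation.* It does. It comes from the printed quantiles within 1.5%, a difference of three or four patients per arm. What it does not follow from is the stated beta.
- *The trial is well short.* That would need a two-sided 90% target: 2 × ((1.96 + 1.28)/0.134)² × 0.2489 = 291.0, i.e. 292 per arm before loss. The text states beta 0.20 and a one-sided alternative, so neither half of that target is stated for the sizing.
- *The trial over-enrols.* That holds only if one-sided 0.05 and 80% power were both intended. The two-tailed analysis rule and the 1.28 each point elsewhere, and the document does not settle it.
- *The loss allowance is a material error.* It is two patients per arm (257 against 259).

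One could also say that the section defines its quantile for a one- or two-sided level and so leaves sidedness open. But 1.64 at alpha 0.05 is one-sided, and so is the stated alternative. Nor can this be left to a statistical analysis plan, since the conflicting values are printed in this document.

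**Conclusion.** The concern holds as an internal contradiction in a stated power and its inputs. Beta 0.20 and power 0.80 are paired with the 90%-power quantile under a wrong label, and one-sided sizing is paired with two-tailed testing. The stated 80% understates the power of the design as sized: by about 9 percentage points on the one-sided basis actually used and about 2 points two-sided (unpooled variance: about 13 and 8 points).

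These figures rest on the plan's assumed rates of 0.767 and 0.533, 10% loss, 231 evaluable per arm, the normal approximation, and a test against the 0.10 margin. They do not show that the trial is too small. They are also not the power of the analyses as now described, which do not use the margin.

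**What to change.** Keep 257 per arm and make these changes.

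1. **Label and power term.** Relabel the second quantile as the one for 1 − beta, and remove the pairing of beta 0.20 with 1.28.
2. **One alpha, one sidedness, in both sections.** Keeping two-sided 0.05 leaves the analysis rule as it is and changes only the sample size paragraph. Keeping one-sided 0.05 means changing the analysis rule as well.
3. **State power for the fixed size.** This avoids printing a recalculated N that differs from the number enrolled. With 257 randomised and 231 evaluable per arm, power for the test against the 0.10 margin is about 82% at two-sided 0.05, or about 89% at one-sided 0.05, with control-rate variance (about 88% and 93% unpooled). Name the variance used.
4. **Reconcile the margin.** Either add a test of the difference in improvement rates against 0.10 to the main-outcome analysis, or say that the margin served only for sizing and that the analysis tests against no difference. Until this is settled, label the power figures as applying to the margin test.

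Minor corrections to the same paragraph: the printed quantiles give 237 rather than 233, and dividing 233 by 0.90 gives 259 rather than 257. Neither calls for more patients.

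The cost is one rewritten paragraph and a sentence or two in the analysis sections. If the margin test is added, that change should be made before unblinding.
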